### Sample size

2.5

This study is a confirmatory clinical trial designed to evaluate the efficacy of modified Ukgan-san compared with placebo in improving Hwabyung symptoms after 4 weeks of treatment. The primary outcome is the Hwabyung Comprehensive Test (HCT) score (16).

Because no previous pharmacological trials have used the HCT score, direct effect size estimates were unavailable. Therefore, the target effect size was determined based on prior randomized placebo-controlled trials of herbal medicines for emotional symptoms such as anxiety and depression, including studies using the Hamilton Anxiety Rating Scale (HAMA), Hamilton Depression Rating Scale (HAMD), and Depression Anxiety Stress Scales (DASS) (17–19). In these studies, standardized between-group effect sizes ranged from approximately d = 0.30 to 0.68, indicating moderate effects. Previous pharmacological studies in Hwabyung patients using the Hwabyung Symptom Scale (HB-S) reported minimal effect sizes (20, 21); however, these studies differed substantially in interventions, indications, and study design, and therefore were not considered appropriate references for the present trial.

Considering the expected therapeutic effects of modified Ukgan-san on neurotic symptoms and excitability, and conventional interpretations of clinically meaningful effects in anxiety and depression research, a target effect size of Cohen’s d = 0.60 was selected for this study.

Using a two-sided significance level of 0.05, statistical power of 80%, and an effect size of d = 0.60, the required sample size was calculated as 44 participants per group (total n = 88). Assuming a dropout rate of 15%, the final target sample size was set at 104 participants, with 52 participants allocated to each group.

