### Randomization and allocation concealment

2.6

Participants will be allocated to either the experimental or control group in a 1:1 ratio using a simple randomization method. The randomization sequence will be generated and maintained using Microsoft Excel by an independent researcher ([name]) who is not involved in participant recruitment, assessment, or data analysis. Access to the randomization sequence will be restricted to the designated study coordinator, and investigators responsible for participant enrollment and assessment will not have access to the allocation sequence.

The manufacturer will prepare the study medication according to the randomization schedule. The prepared study medication will be labeled with a serial number in the UKS-AA-ZZZ format, provided to the principal investigator, and managed by the designated study pharmacist. In this labeling system, AA indicates the site number and ZZZ indicates the sequential number assigned to participants, beginning from 001.

The correspondence table linking the randomization schedule with the serial numbers of the study medication will be sealed and stored in a manner that allows verification of whether the seal has been broken, and access will be restricted to designated study management staff only. When a medication request is received from the investigator for a registered participant, the study pharmacist will assign the study medication sequentially to the participant and will record and manage the participant identification code on the study medication serial number log.

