### Statistical analyses

2.13

The primary outcome is the symptom subscale of the HCT, with higher scores indicating greater symptom severity. Treatment efficacy will be evaluated based on the changes from baseline to Week 4.

Between-group differences will be analyzed using a linear mixed model (LMM). Fixed effects will include group (intervention vs. control), time (baseline, Week 4, and Week 8), and the group × time interaction, with the subject included as a random intercept. The LMM was selected because it appropriately accounts for within-subject correlation in repeated-measures data and allows the inclusion of participants with incomplete data under the maximum likelihood estimation framework, thereby reducing potential bias compared to complete-case analysis.

All efficacy analyses will be conducted according to the intention-to-treat (ITT) principle, including all randomized participants. Missing data will be handled under the assumption of missing at random (MAR) using maximum likelihood estimation within the LMM framework. In this study, reasons for dropout and the occurrence of adverse events will be collected whenever possible, and the MAR assumption was considered appropriate because missingness may be associated with observable factors such as previous measurements, treatment response, and adverse events. In addition, a per-protocol (PP) analysis reflecting adherence and major protocol violations will be performed to evaluate the consistency of the results.

The primary analysis will test the significance of the group × time interaction. A pre-specified contrast will be used to estimate the between-group difference in the mean change at Week 4. A decrease in score represents clinical improvement; therefore, a negative between-group difference in change (Δ intervention − Δ control) that is statistically significant will be interpreted as evidence of treatment efficacy.

Secondary outcomes (anger, depression, anxiety, HRV, and neurotic symptoms) will be analyzed using the same LMM framework. Variables without intermediate measurements, such as depression, anxiety, and HRV, can also be analyzed with LMM; in these cases, random slopes will be omitted and only random intercepts will be included. Contrasts can be specified to examine between-group differences at each time point. To control for multiplicity across secondary endpoints, the p-values will be adjusted using the Holm procedure.

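### The primary Week 4 contrast is an unadjusted change-score comparison: unbiased, but it gives up precision that the baseline HCT score, already collected, could supply

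*Protocol article*

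**What the plan says.** Section 2.13 (Statistical analyses) states the primary model outright: "Fixed effects will include group (intervention vs. control), time (baseline, Week 4, and Week 8), and the group × time interaction", with a random intercept for subject. Baseline HCT is therefore a response. The group term together with the interaction lets the two arms have different baseline means. From this model, "A pre-specified contrast will be used to estimate the between-group difference in the mean change at Week 4", and a significant negative value of intervention change minus control change counts as efficacy. The secondary outcomes use the same framework.

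The article nowhere enters baseline HCT as a covariate or constrains the arms to a common baseline mean. Table 2 shows that HCT is measured at T1, so the information is collected in any case.

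Section 2.5 (Sample size) sets the target: "Using a two-sided significance level of 0.05, statistical power of 80%, and an effect size of d = 0.60", giving 44 per group, and then "Assuming a dropout rate of 15%, the final target sample size was set at 104 participants". The effect size is borrowed from trials on other scales: "In these studies, standardized between-group effect sizes ranged from approximately d = 0.30 to 0.68". Whether the SD behind d is that of scores or of changes is not stated.

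**The concern.** A difference in raw changes subtracts the whole baseline value, which amounts to assuming a slope of 1 of Week 4 on baseline. Under randomisation the arms share the same expected baseline, and using that fact lets the data set the slope. When the two SDs are similar and r is below 1, the best slope is below 1, so the raw change carries avoidable noise.

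At stake is the width of the primary confidence interval in a trial that section 2.5 calls confirmatory and that is sized to about 80% power, with little to spare. A separate SAP may exist, but the article states the model and contrast explicitly. This is a choice it makes, not a detail it leaves open.

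**Working it through.** **Inputs from the document.** Two-sided alpha 0.05, power 80%, d = 0.60, 44 per arm, 15% dropout, 52 per arm randomised (section 2.5); model and contrast (section 2.13).

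**Inputs assumed.** r from 0.3 to 0.8; k = baseline SD / Week 4 SD, taken as 1 and then 0.8. The document gives neither.

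**1. The plan's own figure.** Normal approximation: n per arm = 2(1.960 + 0.842)² / 0.60² = 43.6, so 44. Dropout: 88 / 0.85 = 103.5, so 104. Both reproduce. By the t-test, 44 per arm gives 79.5% power.

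**2. What the contrast estimates.** The planned model was fitted to simulated complete data (44 per arm, three visits). The Week 4 interaction coefficient was −0.60834, and so was the raw difference in mean changes.

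**3. Variance, complete data, k = 1.** In units of the score variance times 2/n:
- planned contrast: 2(1 − r)
- baseline-adjusted: 1 − r²
- ratio, adjusted/planned: (1 + r)/2

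| r | planned | adjusted | ratio |
|---|---|---|---|
| 0.3 | 1.40 | 0.91 | 0.65 |
| 0.5 | 1.00 | 0.75 | 0.75 |
| 0.7 | 0.60 | 0.51 | 0.85 |
| 0.8 | 0.40 | 0.36 | 0.90 |

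**4. With dropout.** Exact generalised least squares for three visits, 52 per arm, 8 per arm lost after baseline (8/52 = 15%). Variances of free versus common baseline mean: 0.06021 v 0.04136 (r = 0.3), 0.04371 v 0.03409 (0.5), 0.02664 v 0.02318 (0.7). Ratios: 0.69, 0.78, 0.87.

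**5. Narrower baseline spread.** With Week 4 SD = 1, the planned variance is 1 + k² − 2rk and the adjusted is 1 − r². The difference is (k − r)², never negative but zero at k = r. At k = 0.8:
- r = 0.3: 0.91/1.16 = 0.78
- r = 0.5: 0.75/0.84 = 0.89
- r = 0.7: 0.51/0.52 = 0.98

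**6. Power, 44 per arm, non-central t, k = 1, complete data.**

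| r | d on change SD: planned → adjusted | d on score SD: planned → adjusted |
|---|---|---|
| 0.3 | 79% → 93% | 65% → 83% |
| 0.5 | 79% → 89% | 79% → 89% |
| 0.7 | 79% → 86% | 95% → 97% |
| 0.8 | 79% → 83% | 99% → over 99% |

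**7. Does the covariance structure matter for the fix?** A random intercept forces equal variances at all visits. In a two-visit approximation with k = 0.8 and r = 0.7 it implies a baseline slope of 2rk/(1 + k²) = 1.12/1.64 = 0.683, whereas the best slope is r/k = 0.875. The variance is then 1 + 0.683² × 0.64 − 2 × 0.683 × 0.56 = 0.534, against 0.52 for the planned contrast: about 3% worse.

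**The case against.** The strongest reply is that nothing promised is lost. The contrast matches the stated aim, change from baseline to Week 4, and is unbiased under randomisation. If d = 0.60 is on the change scale, the trial has the power it was sized for. That stands, and it makes this an improvement rather than an error.

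The size of the gain rests on undocumented inputs. That also stands. A reader might infer from the variance ratios that the trial needs 18–54% more patients (1/0.85 and 1/0.65) to match an adjusted analysis. Those figures are only r = 0.7 and r = 0.3 with complete data and equal variances. With the planned dropout the range is about 15–46%, and with a narrower baseline spread it can be close to zero. Diagnostic and cutoff entry criteria make a narrower spread plausible, though no SDs are given.

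A reader might also point to section 2.6, "Participants will be allocated to either the experimental or control group in a 1:1 ratio using a simple randomization method", as making matters worse. It adds little: blocking would even out arm sizes but not HCT, and only stratifying on HCT would limit HCT imbalance. The pull of a chance baseline difference on the estimate is the same loss seen in a single trial, not a second one.

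Finally, adjustment is not free of downsides in every form. Moving baseline out of the outcomes and into a covariate drops anyone lost before Week 4: section 2.8 ends assessments at withdrawal, and the stated model has no Week 2 level. That conflicts with the commitment in section 2.13 to analyse everyone randomised. A common-baseline model that keeps only the random intercept can lose a little precision (step 7). Both objections stand, and they shape the fix.

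**Conclusion.** The point holds as one of efficiency. The planned primary estimate leaves baseline HCT unadjusted and so has a larger variance than it need have: by the ratios above, 0.65–0.90 for r of 0.3–0.8 with equal variances and complete data, 0.69–0.87 for r of 0.3–0.7 with 15% dropout, and 0.78–0.98 over the same r if the baseline SD is 0.8 of the Week 4 SD.

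The documents do not support the stronger reading that the primary analysis is biased, invalid or underpowered. A shortfall against 80% arises only if d = 0.60 is on the score SD and r is below 0.5 (65% against 83% at r = 0.3). On that scale the gain is small once r reaches 0.7. The change is worth making because the data are already collected, but its benefit cannot be fixed at one number without r and the SDs.

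**What to change.** In section 2.13, for the primary outcome:
- Constrain the two arms to a common baseline mean by dropping the group effect at baseline and keeping group differences at the post-baseline visits.
- Keep baseline HCT in the outcome vector, so that every randomised participant with a baseline score contributes.
- Replace the random intercept alone with an unstructured covariance across visits.
- Name the resulting baseline-adjusted Week 4 difference as the primary estimate.

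Use the same approach for the secondary outcomes. In section 2.5, state which SD d = 0.60 refers to.

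Cost: no extra patients or visits. The model stands in the protocol article and recruitment has started, so a dated protocol amendment before unblinding is needed. With the three visits listed, the unstructured covariance has 6 parameters instead of 2, and the mean model has one fewer.

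### Secondary outcomes: the only contrast named is optional, does not match the primary's difference in change and is not baseline-adjusted; a common-baseline Week 4 contrast would be at least as precise at no cost

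*Protocol article*

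**What the plan says.** All the relevant text is in section 2.13 (Statistical analyses) of the protocol article.

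- **Model.** The fixed effects are group, "time (baseline, Week 4, and Week 8), and the group × time interaction, with the subject included as a random intercept". Baseline is thus one of the response levels, with a separate mean in each arm.
- **Primary outcome (HCT symptom subscale).** "The primary analysis will test the significance of the group × time interaction", and "A pre-specified contrast will be used to estimate the between-group difference in the mean change at Week 4".
- **Secondary outcomes.** "Secondary outcomes (anger, depression, anxiety, HRV, and neurotic symptoms) will be analyzed using the same LMM framework". The only contrast then named for them is: "Contrasts can be specified to examine between-group differences at each time point".
- **Multiplicity.** "To control for multiplicity across secondary endpoints, the p-values will be adjusted using the Holm procedure". The text does not say which contrast, or which visit, supplies the p-value for each endpoint.

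Table 2 (section 2.8) shows that every secondary scale and HRV are measured at T1. Section 2.6 specifies simple randomization and mentions no stratification.

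**The concern.** The primary effect is a difference in change. The one contrast named for the secondary outcomes is, on its ordinary reading, a difference in levels at a visit. The two answer different questions, and they can disagree in a given trial merely because the arms started apart. With simple randomization and about 52 per arm, modest gaps at baseline are likely on at least some scales.

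The baseline value is available for every secondary endpoint, yet the named contrast does not use it for adjustment. The precision lost is lost on the endpoints that must also pass a Holm correction.

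**Working it through.** **Plan's own figure.** Section 2.5 states: "Using a two-sided significance level of 0.05, statistical power of 80%, and an effect size of d = 0.60". The normal approximation gives n = 2(1.96 + 0.842)²/0.60² = 43.6, so 44 per arm and 88 in total. Then 88/(1 − 0.15) = 103.5, so 104, or 52 per arm. The plan's numbers reproduce, and nothing below changes them.

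**What each contrast estimates.** The model was fitted to one simulated complete data set with 44 per arm, three visits and a random intercept:

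- The model's Week 4 between-group contrast was −0.763, equal to the raw difference in Week 4 means.
- The group × time term at Week 4 was −0.696, equal to the raw difference in change.
- They differ by −0.763 − (−0.696) = −0.067, which is exactly the chance baseline gap.

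Having baseline as a response level therefore does not by itself adjust the Week 4 contrast.

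**Chance baseline gap.** In SD units with 52 per arm, its SD is √(2/52) = 0.196. The chance per scale of a gap beyond 0.2 SD in either direction is 31% (0.2/0.196 = 1.02), and beyond 0.3 SD it is 13% (0.3/0.196 = 1.53).

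**How the gap is carried.** Let r be the baseline-to-Week-4 correlation, which the protocol does not give, and assume equal SDs at both visits. A gap g shifts the level contrast by +r·g, the change contrast by −(1 − r)·g, and the adjusted contrast by 0. With g = 0.3, no drug effect and 52 per arm, the conditional SD is 0.196·√(1 − r²). The critical values are 1.96·0.196 for levels and 1.96·0.196·√(2 − 2r) for change. The conditional rejection rates are:

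| r | level | change |
|---|---|---|
| 0.3 | 6.3% | 9.6% |
| 0.5 | 8.5% | 8.5% |
| 0.7 | 10.7% | 7.2% |

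Averaged over all randomizations, both are 5%.

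**Precision.** The variances are (2/n) for levels, (2/n)(2 − 2r) for change and (2/n)(1 − r²) for adjusted. With n = 44 per arm:

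| r | SE level | SE change | SE adjusted | level/adjusted | change/adjusted |
|---|---|---|---|---|---|
| 0.3 | 0.213 | 0.252 | 0.203 | 1.05 | 1.24 |
| 0.5 | 0.213 | 0.213 | 0.185 | 1.15 | 1.15 |
| 0.7 | 0.213 | 0.165 | 0.152 | 1.40 | 1.08 |

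The adjusted variance never exceeds either of the others: 1 − r² ≤ 1, and (2 − 2r) − (1 − r²) = (1 − r)² ≥ 0.

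**Power for a 0.60 SD effect, 44 per arm**, from Φ(0.60/SE − z). The second level, 0.05/10 = 0.005 (z = 2.807), is only an example of a Holm step:

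| r | α = 0.05: level / change / adjusted | α = 0.005: level / change / adjusted |
|---|---|---|
| 0.3 | 80 / 66 / 84% | 50 / 33 / 56% |
| 0.5 | 80 / 80 / 90% | 50 / 50 / 67% |
| 0.7 | 80 / 95 / 98% | 50 / 80 / 87% |

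**The case against.** The strongest reply is that the sentence is permissive. It says contrasts can be specified, while the binding statement sends the secondary outcomes through the primary's model, which contains the group × time interaction. On that reading a difference in change is available for them too. That stands. A reader might infer that the secondary results ignore baseline altogether, but the text does not support this. Even for the level contrast it would be exact only with complete data, because with dropout some baseline information enters through the random intercept.

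A reader might also infer that a between-group test at baseline is planned. No such test is stated; it follows only if the reference to each time point is taken at its most literal.

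Nor is the level contrast biased, and matching the primary would not cure the problem. The change contrast carries a chance gap as well, with the same conditional error at r = 0.5 and a larger one at r = 0.3. Below r = 0.5 the level contrast is the more precise of the two.

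Finally, exact secondary contrasts are commonly left to an analysis plan, and one may exist. Silence on detail is therefore not the point. What remains is that the one contrast the article names is not baseline-adjusted, and that the alternative reading is not adjusted either.

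**Conclusion.** The point holds in a limited form. For secondary outcomes the protocol names an optional level contrast that differs from the primary's measure and, with complete data, leaves baseline unused. Under either reading, level or change, the contrast is unbiased over randomization but sensitive to chance baseline gaps, and it is less precise than a baseline-adjusted contrast. For correlations of 0.5 to 0.7 the excess in standard error is 15% to 40% for levels and 15% to 8% for change.

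These sizes rest on assumed correlations, equal SDs at baseline and Week 4, complete data and a normal approximation. The power figures at 0.005 also rest on an illustrative Holm step. That adjustment is at least as precise as either contrast follows from the variance formulas at any correlation.

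Severity is minor. The point is limited to secondary outcomes, and the correction is a free improvement rather than the repair of an invalid analysis.

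**What to change.** Replace the sentence on secondary contrasts in section 2.13 with wording such as:

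*For each secondary outcome the Holm-adjusted contrast is the between-group difference at Week 4 (Week 8 supportive) from the mixed model with a common baseline mean in both arms (or baseline as a covariate); no between-group contrast is tested at baseline.*

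This also settles which p-value enters the Holm procedure for each endpoint. The cost is one sentence, agreed before unblinding. It needs no further data, visits or participants, and the sample size is unchanged.

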## Discussion

3

This study is a clinical trial designed to evaluate the efficacy and safety of modified Ukgan-san in patients with Hwabyung presenting with neurotic symptoms.

This study was designed to minimize the risk of bias by applying a triple-blind, placebo-controlled, randomized design. In particular, procedures were implemented to reduce expectancy effects and assessor bias that may occur in herbal medicine clinical trials, and the study protocol was developed with reference to the SPIRIT checklist and the RoB 2 assessment tool.

Hwabyung has been described as a culture-related psychiatric syndrome characterized by the coexistence of emotional and somatic symptoms. Accordingly, this study evaluates not only psychological outcomes, including depression, anxiety, anger, and neurotic symptoms, but also physiological outcomes such as heart rate variability (HRV) indices, in order to examine the effects of modified Ukgan-san on the symptoms of patients with Hwabyung from multiple perspectives.

In particular, this study focuses on anger, neurotic symptoms, and excitatory emotional states among the symptom domains of Hwabyung. The clinical practice guidelines for Hwabyung suggest, based on expert consensus, that Ukgan-san may be considered when anger-related symptoms are prominent (1). Therefore, this study aims to evaluate the applicability of modified Ukgan-san, which has been used to alleviate neurosis, neurasthenia, and agitated emotional states, in patients with Hwabyung.

In addition, this study is meaningful in that it explores the potential role of herbal medicine-based interventions as complementary and integrative approaches in the management of mental health conditions associated with Hwabyung. If the efficacy and safety of modified Ukgan-san are demonstrated, it may be considered a complementary therapeutic option for patients with Hwabyung presenting with anger and neurotic symptoms. Furthermore, by accumulating evidence-based interventions for culture-related psychiatric syndromes such as Hwabyung, this study may provide preliminary evidence for future research in the field of cross-cultural psychiatry.

This study has several limitations. First, there is a lack of clearly established diagnostic and evaluation criteria specifically for neurotic symptoms. Therefore, the subscales of the Core Seven-Emotions Inventory were collectively used as supportive reference measures, and improvements in neurotic symptoms were evaluated using the Difficulties in Emotion Regulation Scale. To address this limitation, specific symptom domains related to neurotic symptoms (e.g., depression, anxiety, and anger) were assessed concurrently. In addition, this study was conducted at a single center, and the intervention period was relatively short at 4 weeks. Furthermore, because Hwabyung is closely associated with Korean cultural contexts, caution is warranted when generalizing the findings to other cultural populations.

Future studies should include multicenter clinical trials to improve the generalizability of the findings and long-term follow-up studies to evaluate the durability and safety of modified Ukgan-san treatment. In addition, the development of standardized assessment tools for neurotic symptoms will be necessary.

